## Partner Notification Services

In addition to testing, a limited contact tracing *service* will be provided (referred to as Partner Notification) to our HIV positive participants. Partner notification is a public health service aimed to reduce the spread of HIV and to ensure that HIV seropositive individuals receive timely medical care. Partner notification is offered as a service and is separate from the research activities. The goal of this service is to increase the number of people who may have been exposed to HIV to get tested but is not related to any of the research aims.

Early testing, diagnosis, and treatment for HIV can dramatically reduce the morbidity associated with HIV. Partner notification is a standard method for identifying persons at risk of infection. The term “partners” refers to sex and injection partners. In all cases of partner notification, the identity and confidentiality of the participant is protected. Cards from the Baltimore City Health Department will be used to notify partners that “in the interest of their health, they are urged to attend one of the local Baltimore City health clinics to be tested”.

If a participant reports being HIV positive or tests HIV positive as part of the study, they will be informed about the importance of Partner Notification as a public health approach to stop the spread of HIV and to increase the numbers of people who know their status. They will be offered the following three options, which are strictly voluntary. If participants are concerned about consequences of Partner Notification such as potential violence they will be referred to the Baltimore City Health Department for their assistance in notifying partners.

*Partner Notification Options*

- *Participant initiated*: Participant will be provided with Partner Notification cards, which are based on those used by the Baltimore City Health Department. Participants can deliver these cards to their drug and sex partners who may be at risk for acquiring and transmitting HIV. These cards do not identify the participant as the potential source of HIV.
- *Clinic mailing*: Envelopes and postage will be provided which will enable a participant to mail out these cards to their partners. We would also inform the participant that their name will not included on the notification card.
- Participant can *decline* the above mentioned options. In such cases, participants will be provided with information about services that the Baltimore City Health Department offers for HIV testing and medical care. Participant will also be encouraged to have their partners tested for HIV.

***Randomization***

After approximately 20 individuals have been deemed eligible for the intervention, an intervention group will be scheduled. Eligible participants will be contacted by phone and mail to remind them about the upcoming group session. Attached is the group reminder letter.

On the first day of the intervention, participants who show up will be randomized into the intervention or control group. The Data Manager will assign group membership to each index using a computerized randomization program.

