**Population:**

**Phase 3: Full Trial**

Approximately 500 crack smokers and 500 injectors will be recruited to participate in the longitudinal component of the study (i.e. baseline and follow-up assessments) Of these, approximately 250 crack smokers and 250 injectors with CES-D scores ≥16 will be randomly assigned to either the depression intervention or control condition.

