**Statistical Analysis Plan**

**Phase 3: Full Trial**

Several data analysis methods will be used to examine the longitudinal data as well as evaluate the intervention by comparing the 2 treatment arms.

For all estimates of the prevalence of behaviors, outcomes (e.g., depressive symptoms) in this population, we will weight the observations to reflect the oversampling of individuals with higher levels of depression for follow-up assessments. For all other models, we will not weight the observations. In testing hypotheses, it is often necessary to adjust for potentially influential covariates that are not the primary focus of the hypothesis. In the case of independent variables that are continuous, we will use multiple linear regression or other modeling strategies to account for covariates. When the dependent variable is dichotomous or polytomous, we will use log-linear or logistic models, or similar techniques. Model fitting will be accomplished using techniques such as hierarchical stepwise regression and the score test to compare nested models. Due to the nature of sampling and study design, there may be some clustering of data, such as clustering by geographic area or intervention group, which can bias estimates. When needed, statistical techniques that allow for analysis of clustered data we will use, such as Generalized Estimating Equations (GEE) to analyze data clustered by neighborhoods (Liang et al., 1996) and Hierarchical Linear Models (HLM) (Byrk et al., 1992) to provide additional information about factors attributable to the level 2 variance. In addition to handling clustering, HLM will be used to conduct analysis with consideration of both individual and contextual factors. Analysis of data at different levels presents methodological challenges, namely correlations of residual errors among observations nested in higher-level units. Such built-in correlation of errors in hierarchical models violates the assumption of independent errors in conventional statistical procedures. However, multilevel or hierarchical analysis takes into account the built-in correlation of errors in multilevel data (Peacher et al., 2004). It has been applied to contraceptive studies (Krull et al., 2001;1999), needle sharing (Korff et al., 1992), and condom use (Morisky et al., 2002).

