# Power calculations

# The main outcomes of interest are changes in injection and sexual risk behavior and in level of depressive symptoms. A sample size of 200 in each group is assumed for comparisons of sex risk behaviors and depressive symptoms after two years of follow-up with a 10% attrition rate per year. Only half of the sample will be IDUs, and it is assumed that there will be a sample size of 100 per group with the same attrition rates. There will be approximately 50 cohorts (25 intervention cohorts and 25 control cohorts) of with approximately 8 members with complete data at the end of the two years. The power was calculated for an assessment of intervention effectiveness at the end of the study, when sample sizes will be smallest and thus underestimates likely power for comparisons made earlier in the study. Power calculations were done using NCSS/PASS software. Based on the SHIELD study (IRB# H.30.00.07.17.A), we would expect an average CES-D score of 26.7 and variance of 8.3, given the selection methods proposed in the present study. We estimated power with a 2-sided test, setting the alpha at 0.05, with a total sample size of 400. We expect a small amount of correlation due to intervention group (0.02 in the SHIELD Study). A difference between the two groups post intervention on mean CES-D score of 2.0 provides sufficient statistical power.

|  | **Intercluster correlation** | | |
| --- | --- | --- | --- |
| **Difference in mean CES-D score** | 0.00 | 0.02 | 0.05 |
|  | **Power** | | |
| 2.0 | 0.92 | 0.88 | 0.83 |
| 3.0 | 0.99 | 0.99 | 0.99 |
| 4.0 | 1.00 | 1.00 | 1.00 |

Prior studies suggest a larger effect size for intervention effects on injection as compared to sexual risk behaviors. Consequently, despite the smaller sample size for injection risk comparisons, we expect analyses of the two outcomes to have similar statistical power. We based estimates of expected reduction in risk behaviors on the SHIELD study, creating composite scores for injection risk behavior (needle and cooker sharing and frequency of injecting) and sexual risk behavior (9 risk behaviors). The injection risk score had a mean of 11.6 (SD=4.5). The sex risk composite score had a mean of 1.9 (SD=1.8).

|  | Intercluster correlation | | |  | Intercluster correlation | | |
| --- | --- | --- | --- | --- | --- | --- | --- |
| Diff. in mean injection risk score | 0.00 | 0.02 | 0.05 | Diff. in mean sex risk score | 0.00 | 0.02 | 0.05 |

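### Participants are randomised within recruitment waves, but neither the power section nor the analysis text names the wave. Comparing arms within wave is a cheap, minor gain in precision.

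*Protocol*

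**What the plan says.** Protocol, Randomization: "After approximately 20 individuals have been deemed eligible for the intervention, an intervention group will be scheduled". Allocation is then individual, among those who attend: "On the first day of the intervention, participants who show up will be randomized into the intervention or control group".

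Protocol, Population: "approximately 250 crack smokers and 250 injectors with CES-D scores ≥16 will be randomly assigned to either the depression intervention or control condition", which is about 500 people.

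Protocol, Power calculations: "There will be approximately 50 cohorts (25 intervention cohorts and 25 control cohorts) of with approximately 8 members with complete data". The only correlation allowed for is one attributed to intervention group, 0.02 in the earlier study, with table columns at 0.00, 0.02 and 0.05.

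Protocol, Statistical Analysis Plan: "there may be some clustering of data, such as clustering by geographic area or intervention group, which can bias estimates". Clustered-data methods are to be used where needed, with GEE mentioned for neighbourhoods and hierarchical linear models for level 2 variance. The recruitment wave is not mentioned in either section.

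**The concern.** The wave is the set of people among whom allocation takes place. The two cohorts of a wave share calendar time, season and whatever recruitment effort produced them. Such shared influences cancel when CBT is compared with control inside a wave. If cohort is the only grouping in the model, they stay in the standard error of the arm difference.

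The stake is efficiency, not false positives. Ignoring a shared wave effect makes the reported standard error too large, pushes the true type I error below 5% and gives up some power. All three outcomes are affected: CES-D, sex risk and injection risk. The stated sample leaves little power to spare for the 2-point CES-D difference.

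**Working it through.** **Inputs.** Population: about 500 randomised. Randomization: about 20 eligible per wave. Power calculations: 25 + 25 cohorts, about 8 completers each, 200 per arm (100 per arm for injection risk), 10% attrition a year for two years, CES-D difference 2.0, spread 8.3, ICC 0.02 and 0.05, two-sided alpha 0.05. The spread is called a variance, but the tables make sense only if it is an SD. **Assumption:** the share *f* of the ICC that is common to the two cohorts of a wave is not given, so 0, 50 and 100% are shown.

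**1. Is the pairing implied?** 500 / 20 = 25 waves, which matches 25 cohorts per arm. 20 / 2 = 10 per arm per wave, and 10 × 0.9² = 8.1, which matches about 8 completers.

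**2. The plan's own power figures.** Power = Φ(δ/SE − 1.96), with SE² = 2·SD²·D/n and D = 1 + (m − 1)·ICC. With m = 8, D = 1.00, 1.14, 1.35.
- n = 200 per arm, as stated: 0.674 / 0.617 / 0.545, against the printed 0.92 / 0.88 / 0.83. Not reproduced.
- n = 400 per arm: 0.926 / 0.891 / 0.835. This fits.

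So the CES-D row uses an independent-cohort design effect with no wave term, on twice the stated sample.

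**3. Effect of the wave on the variance.** For a within-wave contrast, D = 1 + (m − 1)·ICC − m·f·ICC. At full sharing:
- ICC 0.02: 1.14 − 0.16 = 0.98. The true SE is √(0.98/1.14) = 0.93 of the reported one, 7% smaller.
- ICC 0.05: 1.35 − 0.40 = 0.95. The ratio is √(0.95/1.35) = 0.84, 16% smaller.

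**4. Power and type I error at the stated design.** 25 waves, 8 per arm per wave, difference 2.0, SD 8.3. Unpaired (48 df) and paired (24 df) t-tests on cohort means were simulated with 40,000 trials per scenario.

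| ICC | f | Power, wave ignored | Power, within wave | Type I error, wave ignored |
|---|---|---|---|---|
| 0.02 | 0 | 0.60 | 0.58 | 0.049 |
| 0.02 | 50% | 0.60 | 0.61 | 0.042 |
| 0.02 | 100% | 0.60 | 0.64 | 0.034 |
| 0.05 | 0 | 0.53 | 0.51 | 0.048 |
| 0.05 | 50% | 0.53 | 0.58 | 0.036 |
| 0.05 | 100% | 0.53 | 0.66 | 0.021 |

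The paired test held its type I error between 0.048 and 0.051.

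**5. Risk composites.** These use the large-sample formula at full sharing. It ignores the lost degrees of freedom and so flatters the gain.
- Sex risk, difference 0.5, SD 1.8, 200 per arm: 0.74 to 0.80 at ICC 0.02, and 0.67 to 0.81 at ICC 0.05.
- Injection risk, difference 1.5, SD 4.5, 100 per arm, 4 per cohort: 0.63 to 0.66 at ICC 0.02, and 0.59 to 0.68 at ICC 0.05.

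**The case against.** A reader might infer that the plan analyses the 50 cohorts as independent. The document does not support that. Its clustering units are examples, its methods apply only where needed, and the model for the arm contrast is left open. A statistical analysis plan that is not shown could include the wave. This part of the objection stands in full.

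A reader might also infer that the printed power rests on the 50 stated cohorts. It does not. The CES-D figures match 400 per arm, that is 50 cohorts of 8 per arm.

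Nor is the wave the only unit that crosses both arms. Individuals are randomised, so neighbourhoods cross them too, and the analysis text already provides for neighbourhood clustering. Some of what a wave shares may be geographic.

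The strongest objection concerns the unknown share. The ICC is described as due to intervention group. Read literally, that is specific to a group and not shared with its partner, which points to a low *f* and little or no gain. Even at full sharing with ICC 0.02, the correlation between paired cohort means is only 0.02 / (0.02 + 0.98/8) = 0.14. On the other side, the control condition is one session of about 90 minutes, so any correlation among control participants probably reflects who was recruited and when. The document does not settle this.

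The pairing is also inferred. Only those who attend are randomised, so no-shows would mean smaller waves, and equal allocation within a wave is not stated.

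What survives is narrower: the allocation procedure creates a natural stratum, neither section names it, and using it costs very little.

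**Conclusion.** The point holds as a minor improvement. Omitting the wave can only make the arm comparison conservative; there is no inflation of false positives. At the plan's expected ICC of 0.02, comparing within wave gains at most about 4 points of power for the 2-point CES-D difference, and loses about 2 if nothing is shared. At ICC 0.05 the most is about 12 points.

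These figures assume 25 waves with 8 completers per arm in each, 8.3 as an SD, and an assumed shared fraction of the ICC. They compare paired with unpaired tests on cohort means, not the mixed model itself.

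It would be wrong to read this as the cause of, or the cure for, low power. The power tables do not match the stated sample size. That is a separate and larger fault, and power for the 2-point difference stays well below 80% with or without the wave.

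**What to change.** In the Statistical Analysis Plan section, state that the arm comparison for CES-D, sex risk and injection risk is made within randomisation wave, with intervention cohort nested in wave. Keep the wave in the model whatever its estimated variance, and use small-sample degrees of freedom. This detail matters: letting the wave variance shrink to zero while using naive degrees of freedom gave a type I error near 0.058 in simulation.

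In Power calculations, describe the cohorts as arising in pairs from about 25 waves. If power is restated, give it over a range for the share of the ICC common to a wave. Correct the sample-size mismatch separately.

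The cost is wording only. The wave should be known from each participant's group start date, so no new data or participants are needed. The price is about 2 points of power if nothing is shared within a wave (0.60 to 0.58 at ICC 0.02).

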***Intervention***

This study will include 1 treatment and 1 control condition. The treatment group is a 10-session skills-building workshop (9 group-based sessions and 1 individual session) based on Cognitive Behavior Therapy. The intervention will focus on developing skills to cope with stress and lower one’s risk for HIV. The intervention group will be led by 2 trained group leaders.

The control group will be a 1 session on standardized HIV information. This session will be led by 1 group leader and last approximately 90 minutes.

***Follow-up Visits***

Follow-up surveys will be conducted at 6 and 12 months after the intervention. All participants who meet the longitudinal study eligibility criteria will be invited to participate in the follow-up visits. Participants will be informed of these follow-up visits during the informed consent process at the baseline visit. Approximately 1 month before their follow-up date, staff will contact clients through phone calls and letters to remind them of upcoming follow-up assessments. A copy of the reminder letter for each follow-up period is included.

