**Methods:**

**Study Design and Rationale**

**Phase 3: Full Trial**

**Phase 3** includes a longitudinal social epidemiological study and a randomized controlled phase II clinical trial. The longitudinal study will include assessments at baseline, 6m, 12m follow-up. A subset of the longitudinal study sample will be eligible for the RCT which will consist of 2 arms- intervention and control condition.

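### Follow-up is dated from the intervention without a defined starting point: the two arms may be assessed at different times since randomisation, and the non-randomised half of the cohort has no date to count from

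*Protocol*

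**What the plan says.** The Follow-up Visits section gives the timing rule: "Follow-up surveys will be conducted at 6 and 12 months after the intervention". The next sentence sets its scope: "All participants who meet the longitudinal study eligibility criteria will be invited to participate in the follow-up visits".

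The Intervention section describes arms of very different length. For treatment: "The treatment group is a 10-session skills-building workshop (9 group-based sessions and 1 individual session) based on Cognitive Behavior Therapy". For control: "The control group will be a 1 session on standardized HIV information". It gives the control session a length of about 90 minutes. It states neither the spacing of the ten sessions nor the date of the control session.

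The Randomization section fixes when allocation happens: "On the first day of the intervention, participants who show up will be randomized into the intervention or control group". A group is scheduled once about 20 people are eligible.

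The Study Design and Rationale section describes the schedule without mentioning the intervention: "The longitudinal study will include assessments at baseline, 6m, 12m follow-up".

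The Population section gives the sizes: "Approximately 500 crack smokers and 500 injectors will be recruited to participate in the longitudinal component of the study", of whom about 250 of each kind are to be randomised.

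**The concern.** There are two separate problems.

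**Between the arms.** Randomisation supports a fair comparison when outcomes are measured at the same time since randomisation. A clock that starts when a participant finishes the assigned sessions starts later in the ten-session arm than in the one-session arm. Any change over time unrelated to treatment would then enter the difference between arms. Such change is plausible: RCT participants are selected on a CES-D of at least 16, and all participants on recent risk behaviour. The smallest CES-D difference in the power table is 2.0 points, so there is little room for a timing artefact. The interim analysis also compares the arms on 6-month endpoints.

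**In the cohort.** Participants who are never randomised attend no session, so a visit date counted from the intervention does not exist for them. Aim 3 analyses all participants together and needs a defined time scale for each of them.

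**Working it through.** The protocol gives no figure for the timing difference, so there is none to reproduce. The check is to work out time since randomisation under each reading of the rule.

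**Inputs from the protocol**
- Treatment arm: 10 sessions. Control arm: 1 session (Intervention).
- Both arms of a group are randomised on its opening day (Randomization).
- Cohort: about 500 + 500 = 1,000. Randomised: about 250 + 250 = 500 (Population).

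**Inputs assumed or inferred**
- The control session is held on the day of randomisation. This is an inference, as no date is given.
- Session spacing is twice weekly (0.5 week) or weekly (1 week). This is an assumption, as no spacing is given.

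**Reading A: each arm counts from its own last session.**

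Offset between arms = (10 − 1) × session gap.
- Twice weekly: 9 × 0.5 = 4.5 weeks = 31.5 days; 31.5 / 30.44 ≈ 1.0 month.
- Weekly: 9 × 1 = 9 weeks = 63 days; 63 / 30.44 ≈ 2.1 months.

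| Assumed spacing | Offset | Treatment arm, 6-month visit | Treatment arm, 12-month visit | Control arm |
| --- | --- | --- | --- | --- |
| Twice weekly | 4.5 weeks | 7.0 months | 13.0 months | 6.0 and 12.0 months |
| Weekly | 9 weeks | 8.1 months | 14.1 months | 6.0 and 12.0 months |

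All visit times are counted from randomisation. Wider spacing lengthens the offset in proportion.

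**Reading B: both arms count from the opening day.** That is the day of randomisation, so the offset is 0.

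**Reading C: both arms of a group count from one shared date, such as the end of the course.** The visits fall later after randomisation, but equally in both arms, so the offset is again 0.

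**Participants with no intervention date.** 1,000 − 500 = 500, or 500 / 1,000 = 50% of the cohort. Anyone eligible for the RCT who does not attend the opening day is also not randomised and has no such date. No reading of the rule gives these participants a visit date. The Study Design section's schedule would serve if counted from baseline, but it does not say so, and the two sections are not reconciled.

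**The case against.** The strongest reply is that the rule is ambiguous rather than wrong. It names neither an end of the course, nor a last session, nor a separate date for each arm. The Randomization section treats the intervention as one event for the whole group, on whose opening day people are allocated to either arm. Read that way, both arms share a date and the offset is zero. This stands: unequal timing cannot be called established.

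It does not remove the point. When the protocol means the start, the Randomization section says so explicitly, which suggests that an unqualified reference to time after the intervention means after it is over. No section mentions a shared group date. A scheduler could reasonably count from each person's own last session, and nothing in the text would prevent it.

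A reader might infer a bias in favour of the intervention, on the argument that scores chosen for being high drift down and the treatment arm is seen later. The protocol does not support this. It gives no rate of change, and regression to the mean from selection occurs largely by the first re-measurement, so steady decline beyond month 6 cannot be presumed. The Rationale also expects relapse among people in more stressful neighbourhoods, which would push the other way.

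A reader might also count the non-randomised half as evidence against the arm comparison. They belong to neither arm, so they bear only on the cohort analyses.

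**Conclusion.** The point holds as a badly fixed time origin. Two parts are certain from the text: the starting point for the two arms is undefined, and the rule cannot be carried out for about half the cohort.

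Unequal timing between the arms is the ordinary reading but is not proven. If it applies, the treatment arm is assessed about 4.5 to 9 weeks later after randomisation than control. This rests on counting from each arm's own last session, on a control session held on the day of randomisation, and on sessions once or twice weekly. Under the other two readings the difference is zero. The protocol gives no basis for the size or direction of any resulting bias in CES-D or risk scores.

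The protocol should be changed. Visit scheduling is set there, and a later analysis plan could model actual visit times but could not realign visits already made.

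**What to change.** In Follow-up Visits, replace the present rule with two stated origins:
- **Both arms:** 6 and 12 months from the date of randomisation. Under the Randomization section this is the same day for both arms of a group, so the offset is zero by construction.
- **Non-randomised participants:** 6 and 12 months from the baseline visit.

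Amend the Study Design and Rationale section to name the same origins.

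The cost is about one sentence in Follow-up Visits, a matching edit in Study Design, and a change to the scheduling database. The downside is that the treatment arm is assessed somewhat sooner after its last session than if visits were counted from completion. One difference remains for Aim 3. Randomised participants wait between baseline and randomisation while a group forms, so their visits will still fall later after baseline than those of non-randomised participants. Recording actual visit dates lets the cohort analyses use time since baseline.
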